### Data management

2.8

Patient data will be coded and the key to the codes will be safeguarded by the secretary of the randomization centre of the Maastricht University. These codes are unknown and not accessible for the researchers. Outcomes of questionnaires and Activ8 will be collected by the assessing physiotherapist. Losses‐to‐follow‐up and respective reasons will be recorded. The researchers collect the data from the assessors every month and enter the data in an electronic database. Access to the data obtained in this research will be restricted to the researchers involved in the collection and analysis of the data. The handling of personal data complies with the General Data Protection Regulation (GDPR) (EU, 2018). Study files will be kept for 15 years.

### Statistical methods

2.9

To analyse the data SPSS version 25.0 (IBM SPSS, Chicago, IL, USA) will be used. For demographic data descriptive statistics will be used and normality assumptions for the variables will be checked. An intention‐to‐treat analysis will be used for the main outcome. To correspond to the primary aim of the study, outcomes of the Activ8 will be dichotomized into adherent and not adherent patients in the intervention and control group. The Chi^2^ test will be used to investigate if there is a significant difference in the proportion of adherent patients to the activity advice between the intervention and control group after one, six and 12 weeks, and if there is a significant difference in the proportion of adherent patients between patients who experienced social support or not on the social support scale after 12 weeks. A Time Series Analysis will be used to present changes over time in perceived illness beliefs of patients and partner/friend. To understand whether illness beliefs influence adherence, Pearson's r between outcomes of the IPQ‐S at baseline and after 12 weeks and (non)adherence measured by the Active8, will be calculated, and linear regression will be used for modelling the relationship between these outcomes. To assess the correlation between attitude and intention to physical activity (MAI) and adherence at 12 weeks, Pearson's will be calculated, and linear regression will be used for modelling the relationship between these outcomes. Influence of age, gender, education level, comorbidity (CIRS), pain (VAS) and disability (QBPDS) on adherence, will be estimated by multiple regression analyses. A *p* value of <0.05 will be considered statistically significant.

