During the first meeting all physiotherapists will be informed about the Dutch guideline for low back pain (Staal et al., 2013) and state of the art knowledge, to provide that treatment during the study will be in accordance with the guideline. Before the second meeting participating physiotherapists will be divided into three groups: in every clinic, an Assessor Physiotherapist (AP), an Intervention Group Physiotherapist (IGP) and a Control Group Physiotherapist (CGP) is needed. The second meeting will be for AP's, IGP's and CGP's separately. The AP's will be trained in knowledge about the study, inclusion criteria, exclusion criteria, informed consent, standardized intake forms and assessments. They will be trained how to communicate about the study in a positive manner to the patient and partner/friend. It will be explained to the physiotherapists how to adhere to the allocation procedure and how to register all investigational procedures and the use of the activity monitor. Participating CGP's will be instructed on the background and rationale of the study, treatment of illness beliefs, the activity advice, and the use of the activity monitor. Participating IGP's will be instructed on the same elements with an additional short course on how to motivate the patient and their partner/friend in organizing social support. Some participating physiotherapists are students Orthopaedic Manipulative Physical Therapy at the Rotterdam University of Applied Sciences, Rotterdam, The Netherlands. They participate in this study as APs where they must conduct a management assignment as part of their Master of Science educational program.

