#### Baseline information

2.3.1

At baseline age, gender and education level will be registered.

To assess whether comorbidity influence adherence to an activity advice the medical burden of chronic illness is assessed with the Cumulative Illness Rating Scale (CIRS) (Appendix 1). The CIRS ranges from 0 (no illness) to 52 points and is a valid and reliable scale to measure comorbidities in clinical research (de Groot, Beckerman, Lankhorst & Bouter, 2003; Fortin et al., 2005).

It is hypothesised that overweighted/obese patients are protentional physical inactive. BMI of the patient will be calculated and categorized according to the WHO criteria (WHO, 2000).

It is hypothesised that the number of recurrences of low back pain influence adherence to an activity advice negatively, therefore, the number of recurrences of periods of low back pain will be noted.

To assess whether perceived pain and/or disability influences adherence to the activity advice, the visual analogue scale (VAS) for pain and the Quebec Back Pain Disability Scale (QBPDS) for disability will be used at baseline, both of which have been validated for assessing pain and disability (Bijur et al., 2001; Boer et al., 2004; Chapman et al., 2011; Smeets, Köke Lin, Ferreira & Demoulin, 2011) (Appendix 1).

Patients who refuse to enter the study will be asked to fill in the questionnaire at baseline (Appendix 1). The refusal questionnaire (RQ) is a study specified questionnaire collecting 13 reasons of refusal for entering the study (Barnes et al., 2012; Barratt et al., 2013; Williams et al., 2007).

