### Assignment of interventions

2.7

It is hypothesised that patients in the intervention group adhere better to the activity advice than patients in the control group. It is also hypothesized that patients having a BMI >25 and patients experiencing >3 episodes of NSLBP are potentially more inactive and non‐receptive to the interventions on adherence. To prevent influence of these factors on study outcomes, stratification is applied on these variables. Therefore, a concealed randomization sequence is prepared by the randomisation centre of the Maastricht University. Randomization will be performed with a block size of four, with strata for BMI (<25, >24) and number of previous episodes of low back pain (2–3, >3).

Investigators, patients, partners or friends and participating physiotherapists are blinded to the allocation and outcomes. To prevent that patient and their partners/friends of both groups will meet in the waiting room appointments of patients treated in the intervention or control group in the same private practice must be planned on different days or sections of the day. Physiotherapist are blinded for participating in the intervention group or control group. To ensure blinding of the physiotherapists, where their training is separate, it will be emphasized not to communicate about the interventions to each other during the investigation period.

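### The primary chi-square ignores the BMI and episode strata used in randomisation, which enter no stated analysis, and takes no account of therapists nested within arm

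*Protocol article*

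**What the plan says.** - **Primary test.** Section 2.9 dichotomises the activity-monitor result and applies a chi-square test "to investigate if there is a significant difference in the proportion of adherent patients to the activity advice between the intervention and control group" after 1, 6 and 12 weeks. It names no stratified or adjusted version. Significance is judged by p below 0.05, and no confidence interval is mentioned.
- **Randomisation.** Section 2.7 (Assignment of interventions) uses blocks of four within strata formed by BMI (two levels) and previous episodes (2–3 or more than 3), which makes four strata. The reason given is: "To prevent influence of these factors on study outcomes, stratification is applied on these variables".
- **Prognostic expectation.** Section 2.3.1 (Baseline information) adds the hypothesis that "the number of recurrences of low back pain influence adherence to an activity advice negatively".
- **Multiple regression.** The covariates listed in section 2.9 are those in "Influence of age, gender, education level, comorbidity (CIRS), pain (VAS) and disability (QBPDS) on adherence". BMI and number of episodes are not among them.
- **Therapists.** Section 2.1 (Participants) plans 20 practices and says that in every clinic "an Intervention Group Physiotherapist (IGP) and a Control Group Physiotherapist (CGP) is needed". No section mentions a therapist or practice term in the analysis or the sample size.

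**The concern.** Two features of the design are not carried into the analysis.

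First, stratified randomisation balances the arms on BMI and episodes. An unstratified chi-square computes its variance as if that balance had arisen by chance. If the factors predict adherence, the variance is too large: the test rejects too rarely under the null and gives away some of the precision that stratification was meant to buy. The article itself supposes that the factors matter, and it states one hypothesis, on recurrences, for which it names no analysis.

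Second, each treating therapist delivers one arm only. The intervention consists of therapist-led discussion, so outcomes of patients seen by the same therapist may be correlated. Differences between therapists then add to the variance of the arm comparison. A chi-square treats all patients as independent and leaves that variance out, so it may reject too often.

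At stake are the calibration of the primary p-value, which is the article's only decision rule, and a modest amount of power.

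**Working it through.** **Inputs from the article.** 142 evaluable patients (163 recruited), 80% power, p < 0.05 (taken as two-sided), 20 practices, one intervention and one control therapist per clinic, four strata, blocks of four.

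**Assumptions, because the article gives no figure.** Therapist intraclass correlation (ICC) 0.01 to 0.10; odds ratio (OR) of each stratification factor with adherence 1, 2 or 3; adherence about 40%; treatment OR 2.7 in the power example.

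**Step 1. The article's own figure.** For a chi-square with 1 degree of freedom, 5% alpha and 80% power, the noncentrality needed is 7.849. If medium is read as w = 0.3, N = 7.849 / 0.3² = 87.2, so 88, not 142. Conversely, 142 corresponds to w = √(7.849 / 142) = 0.235. At w = 0.3, 142 patients give about 95% power. The stated 80% at 142 is therefore not used as a baseline below.

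**Step 2. Ignoring the strata, no clustering.** Simulation with N = 142, four strata, blocks of four and 20,000 trials per setting (Monte Carlo standard error near 5%: √(0.05 × 0.95 / 20,000) = 0.15 percentage points). The plain chi-square is compared with a Mantel-Haenszel test over the four strata.

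| OR per factor | Type I error, plain | Type I error, stratified | Power, plain | Power, stratified |
|---|---|---|---|---|
| 1 | 5.0% | 5.0% | – | – |
| 2 | 4.6% | 5.1% | 80.7% | 81.3% |
| 3 | 3.7% | 4.9% | 74.9% | 78.0% |

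The power figures belong to the assumed treatment OR of 2.7. Only the comparison within a row is informative: a loss of 0.6 points at OR 2 and 3.1 points at OR 3.

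**Step 3. Ignoring therapists, no strata effect.** With 20 × 2 = 40 therapists, the mean caseload is m = 142 / 40 = 3.55. Design effect DE = 1 + (m − 1) × ICC. Actual type I error = 2 × [1 − Φ(1.96 / √DE)]. For ICC 0.05: DE = 1 + 2.55 × 0.05 = 1.1275, 1.96 / √1.1275 = 1.846, type I error 6.5%. For uneven caseloads with coefficient of variation (CV) 0.6, DE = 1 + ((1 + 0.6²) × m − 1) × ICC.

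| ICC (assumed) | DE, equal caseloads | Type I error, equal | Type I error, CV 0.6 |
|---|---|---|---|
| 0.01 | 1.026 | 5.3% | 5.4% |
| 0.02 | 1.051 | 5.6% | 5.9% |
| 0.05 | 1.127 | 6.5% | 7.3% |
| 0.10 | 1.255 | 8.0% | 9.6% |

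Simulation with the ICC set on the latent logistic scale gave similar values for equal caseloads: 5.8%, 6.7% and 8.3% at 0.02, 0.05 and 0.10. A practice effect shared by both arms left type I error at 5.0%, so the therapist level is the one that matters.

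**Step 4. Both together.** At ICC 0.05 with uneven caseloads, the plain chi-square has type I error 6.7% (OR 2 per factor) or 5.7% (OR 3). The stratified test without a therapist allowance has 7.2% or 6.9%. Stratifying alone therefore removes the conservative offset and leaves the clustering part exposed.

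**The case against.** The strongest reply is that the size is small and unknown. With about 3.5 patients per therapist, an ICC of 0.01 to 0.02 moves type I error only to 5.3–5.6%. The strata loss at OR 2 is under one percentage point of power, and the two omissions pull in opposite directions. This stands as a limit on size. It does not justify the test, because the offset depends on two unknown quantities happening to cancel.

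Some of the hypotheses are also narrower than they first look. The baseline section expects overweight patients to be inactive; it does not say that BMI lowers adherence. The section on assignment suggests that some patients may be less receptive to the interventions, which is effect modification, and main effects in a regression would not test it. The secondary objectives in the Introduction list neither BMI nor episodes, so the regression list agrees with them. What remains is that both factors were stratified on to protect the outcome and then left out, and that the recurrence hypothesis has no stated analysis.

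Four stronger readings are tempting but not supported:

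- A reader might infer that the trial's confidence interval is miscalibrated. The article plans none.
- A reader might infer that clustering pulls power below the stated 80%. That needs 80% at 142 patients to be right for the planned test, and Step 1 does not reproduce it.
- A reader might infer that therapist differences bias the effect estimate. With about 20 therapists per arm they add variance; nothing in the article shows a systematic difference.
- A reader might infer that the two therapist roles should have been allocated at random. That would be a design change, and the analysis point does not depend on it. The figure of 40 therapists is itself inferred from the staffing requirement.

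**Conclusion.** The point holds in a limited form. The article itself fixes the test, the covariates and the significance rule, so this is not detail left to an analysis plan. On its own premise that BMI and episodes matter, the unstratified chi-square is conservative and somewhat less powerful than a test over the randomisation strata. The therapist structure may make the same test anti-conservative. The net result at an assumed ICC of 0.05 with uneven caseloads is a type I error of about 5.7–6.7%. All sizes rest on assumed ICCs, prognostic odds ratios and adherence rates. Miscalibration is therefore possible and probably modest, not established. The case for change rests on the mismatch between design and analysis and on the low cost of removing it.

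**What to change.** 1. Make the primary analysis at week 12, the time point used in the sample size section, a logistic regression of adherence on arm, BMI stratum and episode stratum. A Mantel-Haenszel test over the four strata is an acceptable alternative. Use the strata as recorded at randomisation.
2. Report the adjusted effect with a 95% confidence interval, and keep the plain chi-square as a sensitivity analysis.
3. Allow for therapist with generalised estimating equations and cluster-robust standard errors with a small-sample correction, at least as a sensitivity analysis. Nested random intercepts for practice and therapist are less suitable, because with about 3.5 patients per therapist they may not converge.
4. Add number of episodes and BMI to the multiple regression.

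**Cost.** Slightly more analysis work, a model less simple than a 2×2 table, and possibly a slightly wider interval once therapist is allowed for. No new patient data are needed: BMI and episodes are already collected. The analysis file must identify the treating therapist, or practice and arm, which amount to the same if each clinic has one therapist per arm.

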**Methods:**

In a randomized controlled clinical trial, in private physiotherapy practices in the Netherlands, patients ≥18 years presenting with at least a second episode of nonspecific low back pain will be randomized over two groups: activity advice and social support as an add‐on to usual care versus usual care alone. The primary outcome measure is adherence to an activity advice measured by an activity monitor at 1, 6 and 12 weeks. All other objectives will be measured by questionnaires.

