Social support is known as one of the most important factors predicting physical health (Oraison & Kennedy, 2019). While various definitions of social support have been proposed in the literature, most research recognizes social support as the help perceived (i.e., emotional, practical) from others in social networks (Oraison & Kennedy, 2019). In this study, the influence of social support on adherence to an activity advice will be investigated. For the purpose of this study, it is hypothesized that organizing social support by a partner or friend will be a potential treatment option to increase adherence to a physical activity advice. This intervention fits the context of the new health definition where health is defined ‘as the ability to adapt and to self‐manage, in the face of social, physical, and emotional challenges’ (Huber, 2014).

There is evidence indicating that illness beliefs predict health behaviour and activity limitations in low back pain. To minimize negative influence of maladaptive illness beliefs on adherence to a physical activity advice in patients with low back pain (Siemonsma et al., 2013), in this randomized controlled trial, treatment of illness beliefs is added.

Because evidence on clinical barriers is conflicting and limited, influence of confounding factors, such as age, gender, education level, pain and disability, comorbidity, and patient's intention and attitude to physical activity will also be studied. It is hypothesised these factors influence adherence.

The primary objective of this study is to investigate if patients with low back pain randomised to receive social support adhere better to an activity advice than patients randomised to the control group.

Secondary objectives are; whether patients with low back pain perceiving social support during physiotherapy treatment adhere better to an activity advice compared to patients with low back pain without perceiving social support during treatment, and, if age, gender, education level, pain and disability, treatment of illness beliefs, comorbidity and attitude and intention to physical activity influences a patient's adherence to an activity advice.

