#### Primary outcome

2.3.2

Adherence to the activity advice according to the DSHPA is the primary outcome measure and will be measured by a 3D accelerometer (Activ8, 2M engineering, Valkenswaard, the Netherlands). During the assessment periods at one, six‐ and 12‐week patients are instructed to wear the Activ8 every day during one week. The number of days per week patients have walked or cycled according to the advice will be counted. Cut‐off for adherence will be set at a minimum of 5 times per week of at least 30 min walking and/or cycling. The Activ8 system is a valid instrument to quantify body postures and motions (Fanchamps et al., 2018). For this study only the walking and cycling activities recorded by the monitor will be used for analyses.

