### Sample size

2.5

To determine a medium effect size of the intervention on adherence to the activity advice after 12 weeks in the intervention group compared to the control group, Power G sample size calculation is performed. With an alpha of 0.05% and a power (1‐beta) of 80%, 142 patients are needed. With an expected overall drop‐out rate of 15%, a total of 163 patients is needed.

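### Adherence in the same patients at weeks 1, 6 and 12 is analysed by three separate unadjusted chi-square tests, which cannot show whether the arm difference changes over time

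*Protocol article*

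**What the plan says.** The abstract of the protocol article defines the primary outcome as "adherence to an activity advice measured by an activity monitor at 1, 6 and 12 weeks". Under Primary outcome (2.3.2), in each of the three assessment periods "patients are instructed to wear the Activ8 every day during one week", and the reading is then made binary: "Cut‐off for adherence will be set at a minimum of 5 times per week of at least 30 min walking and/or cycling".

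Statistical methods (2.9) compares the arms by chi-square, the target being "significant difference in the proportion of adherent patients to the activity advice between the intervention and control group after one, six and 12 weeks", with p<0.05 as the criterion. No covariate and no model across weeks is named for this comparison. The only analysis over time in that section concerns another variable: "A Time Series Analysis will be used to present changes over time in perceived illness beliefs of patients and partner/friend".

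Three other places bear on the point:

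- Assignment of interventions (2.7) stratifies the randomisation by BMI and by number of previous episodes, because both are expected to affect activity and response.
- Sample size (2.5) is set on the "effect size of the intervention on adherence to the activity advice after 12 weeks in the intervention group compared to the control group". The sentence that opens "With an expected overall drop" then allows for 15% loss, raising 142 patients to 163.
- The primary objective in the Introduction is whether patients "randomised to receive social support adhere better to an activity advice than patients randomised to the control group". It does not mention change over time.

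**The concern.** A chi-square test takes one cross-section at a time. Three of them give three answers about the arm difference and none about how those answers relate. If week 1 is significant and week 12 is not, that does not show that the effect was larger at week 1.

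The comparison is tempting in this trial because the three readings fall at different stages of delivery. According to Timeline (2.4), the first monitor week ends before the second consultation, the intervention physiotherapist contacts the partner or friend in weeks 6 and 10, and the support schedule covers the months ahead. A report with three p-values will have to say how they fit together, and the stated analysis gives no estimate for doing so.

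Two smaller losses come with the same choice. The tests make no use of a patient's other monitor weeks, and they ignore the two stratification factors that the protocol itself considers influential.

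**Working it through.** **The plan's own figures.** 142 × 1.15 = 163.3, which gives the stated 163. With 15% lost, 163 × 0.85 = 138.55 remain. The 142 could not be reproduced from the stated inputs: the effect is called medium without a number, and a conventional medium effect of w = 0.3 in a 2×2 chi-square with 80% power and two-sided alpha 0.05 gives 88. Nothing below depends on the 142 being right.

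**Assumptions.** The protocol gives no adherence rates and no correlation between weeks. Assumed here are the same true effect at all three weeks, 80% power at each week, and a correlation ρ between any two of the three test statistics of 0.3, 0.5 or 0.7.

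**Step 1: chance disagreement.** The three z statistics are taken as trivariate normal with mean 1.96 + 0.84 = 2.80, unit variance and common correlation ρ. A test is significant when |z| > 1.96. By simulation:

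| ρ | Three tests not all in agreement | Week 1 significant, week 12 not |
|---|---|---|
| 0.3 | 40% | 13% |
| 0.5 | 34% | 11% |
| 0.7 | 26% | 9% |

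The mirror pattern, week 12 significant and week 1 not, is equally frequent. With 70% power at each week and ρ = 0.5, disagreement is 43%.

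**Step 2: check with binary data.** Three correlated binary outcomes were simulated with 71 per arm (142/2, assuming 1:1 allocation), the same true rates at every week and latent correlations of 0.3 to 0.8. At 30% v 53%, about 80% power per test, the tests disagree in 31% to 42% of trials, and each one-directional pattern occurs in 10% to 14%. At 30% v 50%, about 69% power, disagreement is 40% to 58%. The rates are illustrations.

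**Step 3: precision at week 12.** Suppose that the 15% lost are excluded from the week-12 test but have both earlier readings. With correlation ρ between weeks, the two earlier readings explain R² = 2ρ²/(1 + ρ) of the week-12 variance. The effective sample is then 163 × 0.85/(1 − 0.15 × R²):

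| ρ | R² | Effective sample | Gain over 138.55 |
|---|---|---|---|
| 0.3 | 0.138 | 141.5 | 2.9 |
| 0.5 | 0.333 | 145.8 | 7.3 |
| 0.7 | 0.576 | 151.7 | 13.1 |

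**Step 4: what an arm-by-week contrast can detect.** If the effect halves between two weeks, the z means are 2.80 and 1.40. Their difference has mean 1.40 and standard deviation √(2(1 − ρ)), which is 1.18 at ρ = 0.3 and 0.775 at ρ = 0.7. The standardised difference is 1.18 or 1.81, so power at two-sided 5% is about 22% or 44%.

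**The case against.** The strongest reply is that no stated question goes unanswered. The objective is whether the supported arm adheres better, and a between-arm chi-square at a given week is a valid test of that at that week. Correlation between a patient's weeks does not invalidate any single test, and the weekly tables do show both arms' proportions. The condensed article may also stand in front of an analysis plan with a longitudinal model. All of this stands, and it limits the point to an improvement on the method that the article names.

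A reader might infer two stronger things.

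- **That the trial will report a fading or delayed effect.** The protocol has no such objective and no rule for comparing p-values across weeks. The 26% to 40% is the chance that the p-values disagree, not the chance of a false claim. It also assumes a constant effect, and the staged delivery gives no particular reason to expect one.
- **That a patient lost by week 12 contributes nothing.** Section 2.9 states intention-to-treat for the main outcome without saying how missing weeks are handled, so exclusion is an assumption. The 15% is an overall rate, and earlier loss would shrink the gain in Step 3.

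It is also fair that the arm-by-week contrast will often be inconclusive (Step 4). An interval that shows this is still a sounder basis than comparing significance labels.

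The use of p<0.05 at three weeks without a decisive week is a separate matter. Naming week 12 as primary would settle that, but would not provide an estimate of change.

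**Conclusion.** The concern holds in a limited form. The stated method is valid week by week, but it leaves out the within-patient link and the stratification factors and estimates nothing about change. The three p-values therefore cannot carry a claim of fading or building: under a constant effect they would disagree in about 26% to 40% of trials (80% power per week, ρ from 0.7 to 0.3), and more often at lower power. The loss of week-12 precision is modest, about 3 to 13 effective patients, and conditional on exclusion of lost patients whose two earlier readings are available. The effect of leaving out the strata cannot be sized from the document. No stated objective is defeated; this is a low-cost improvement to the primary analysis.

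**What to change.** In section 2.9, or in the analysis plan if it is still open:

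1. Replace the three chi-square tests with one repeated-measures logistic model containing arm, week, arm by week, BMI stratum and episode stratum, using every available monitor week.
2. Take the week-12 contrast, the week used for the sample size, from this model as a marginal risk difference with 95% CI. A mixed logistic model needs averaging over patients to give this.
3. Base any statement on change over time only on the arm-by-week contrast with its CI, and say in advance that its power is low.
4. Keep a table of the plain proportions adherent by arm and week.

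No new data or patients are needed. The cost is wording, a somewhat more complex analysis and an explicit missing-data assumption: missing at random for a likelihood-based mixed model, and a stronger one for ordinary GEE. The two are not interchangeable here, so the choice should be stated.

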### Timeline

2.4

Eligible patients will be recruited for the study together with their partner or friend by the assessing physiotherapist and will receive information about the study. If patients and partners or friends decide after 1 week of consideration they want to be included in the study, written informed consent will be asked to the patient and partner or friend and base‐line assessment of the patient and partner or friend will be performed (Appendix 1). After base‐line assessment the assessor explains to the patient that further treatment will be performed by an IGP or CGP. The patient will be contacted within 2 days for an appointment with either the IGP or CGP. The patient and partner/friend will be instructed to come both to the next two appointments. The assessor contacts the randomization centre. The randomisation centre allocates the patient for IGP or CGP and informs the assessor. The assessor instructs the IGP or CGP to make the next appointments with the patient and their partner/friend.

After the first intervention on illness beliefs with or without organizing social support, treatment will be applied according to the Dutch guideline for low back pain (Staal et al., 2013). In both groups' patients are instructed in executing the activity advice in accordance with the DSHPA and to wear a move monitor for 1 week (Hildebrandt et al., 2007). In the group in which the social support is given, the partner/friend will be asked to make a week schedule of times, activities, and contact‐control moments for the coming months.

At the end of the week the activity monitors will be returned, and questionnaires will be filled out. The second intervention on illness beliefs with or without organizing social support takes place and treatment will be applied according to the Dutch guideline for low back pain (Staal et al., 2013). After six‐ and 12‐weeks patients will be invited by the assessors to wear the Active8 for one week and to fill in the questionnaires. During the study period the IGP contacts the partner/friend in week 6 and 10 to evaluate whether social support was given. At the last appointment also the partner or friend will be invited and asked to fill in questionnaires. Enrolment of the study is shown in the flow diagram (Figure 1).

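### Week 12 drives the sample size but is not declared primary: adherence is tested between arms at weeks 1, 6 and 12, each at p<0.05, with no order or adjustment

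*Protocol article*

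**What the plan says.** **Outcome.** The abstract (Methods) states: "The primary outcome measure is adherence to an activity advice measured by an activity monitor at 1, 6 and 12 weeks". Section 2.3.2 (Primary outcome) lists the same three assessment periods and sets the cut-off that makes each one a yes/no result. Neither place ranks the weeks. The primary objective, in the abstract and the introduction, names no week.

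**Analysis.** Section 2.9 links the dichotomised monitor result to the primary aim. It then applies a chi-square test to the proportion adherent "between the intervention and control group after one, six and 12 weeks". One threshold covers everything: a p "value of <0.05 will be considered statistically significant". No order of testing or adjustment is given.

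**Sample size.** Section 2.5 is built on a medium effect "of the intervention on adherence to the activity advice after 12 weeks". For the comparison of the randomised arms, this is the only place that singles out one week.

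**Timing.** Under 2.4 (Timeline), the monitor is first worn for a week after the first session and is returned at the end of that week. Then "The second intervention on illness beliefs with or without organizing social support takes place".

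**The concern.** The outcome and analysis sections describe three tests of equal standing, while the design calculation rests on one. Two things follow.

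- **Error rate.** A threshold of 0.05 per test holds the error at 5% for each week. It does not hold it at 5% for the primary question if any of the three weeks can answer that question.
- **Conflicting results.** The three weeks may disagree, for example with a difference at week 1 and none at week 12. The article does not say which result then answers the primary objective.

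The weeks are also not interchangeable. The week-1 measurement is complete before the second session is held, so it reflects partial delivery of the intervention. As 2.9 is written, it has the same standing as week 12.

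**Working it through.** **Inputs**
- Between-arm tests of the primary outcome: 3 (2.9).
- Threshold: 0.05 for each (2.9). A chi-square test on a 2×2 table is two-sided by nature.
- Correlation between the three test statistics: not given. It is assumed, and a range is shown.
- Patients per arm for the simulation: 142/2 = 71, assuming 1:1 allocation (two arms, blocks of four; no ratio is stated).

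**The plan's own figures.** The article states no family-wise error rate, so there is none to reproduce. Its stated size is "of 80%, 142 patients are needed", for a medium effect that is given no numerical value. Section 2.5 prints alpha as 0.05%; it is read here as 0.05, as in 2.9. A 2×2 chi-square test with Cohen's w = 0.3 and 80% power needs 88 patients, whereas 142 corresponds to w of about 0.235. The 142 therefore cannot be reproduced from what is stated. That is a separate matter and does not affect the error rates below.

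**Step 1: independent tests, either direction.** 1 − (1 − 0.05)³ = 1 − 0.8574 = 0.143. The Bonferroni bound is 3 × 0.05 = 0.15.

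**Step 2: independent tests, false claims of benefit only.** 1 − (1 − 0.025)³ = 1 − 0.9269 = 0.073, against 0.025 for one test.

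**Step 3: correlated tests.** The chance that at least one of three equally correlated standard normal statistics passes 1.96 under the null (1,000,000 draws per row):

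| Assumed correlation | Either direction | False benefit only |
|---|---|---|
| 0 | 14.3% | 7.3% |
| 0.3 | 13.6% | 6.8% |
| 0.5 | 12.6% | 6.3% |
| 0.7 | 10.9% | 5.5% |
| 0.8 | 9.9% | 4.9% |
| 0.9 | 8.4% | 4.2% |
| 1 | 5.0% | 2.5% |

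If correlation decays with time (first-order autoregressive), the two-sided figure is 12.9% at 0.5 and 10.3% at 0.8.

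**Step 4: the actual test.** Three uncorrected chi-square tests were simulated at 71 per arm, with true adherence of 30% or 50% in both arms (assumed), over 40,000 trials. They gave 12–15% for within-patient correlations from 0 to about 0.64. The upper end slightly exceeds 14.3% because each test rejects a little more than 5% of the time at this size: with 5.3% per test, 1 − 0.947³ = 0.151.

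**Step 5: remedies compared.**
- *Week 12 as the only primary test:* two-sided error 0.05, with 142 unchanged.
- *All three kept as primary with Bonferroni:* 0.05/3 = 0.0167 per test. Family-wise error is 4.9% at correlation 0, 4.4% at 0.5 and 3.6% at 0.8. For an effect with 80% power at 0.05, the standardised effect is 1.960 + 0.842 = 2.802 and the new critical value is 2.394. Power per test is then Φ(2.802 − 2.394) = Φ(0.408), about 66%.

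**The case against.** **Week 12 is already the anchor.** Section 2.5 sizes the trial on it. Section 2.9 also uses 12 weeks for the perceived-support comparison and for the attitude and intention analysis. A reader might infer that the plan has no primary time point at all; 2.5 does not support that. What stands is narrower: the sections that define the outcome and the test do not say what 2.5 implies.

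**No any-week rule is written.** A reader might infer that one significant week is enough to claim success. The article does not say so; it gives a threshold per test and is silent on which pattern across the weeks counts. This objection stands, so the inflated error is conditional on that reading. The text does not exclude the reading either.

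**The two-sided figure overstates the claim at issue.** The objective is directional: better adherence with social support. The 8–14% includes false findings of harm. For false benefit the absolute figure is about half as large. The baseline halves too, so the inflation remains roughly two- to threefold for correlations from 0.8 to 0.

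**Independence is implausible.** The same patients are measured three times, so the upper end is the least likely. This is fair, and it is why the range extends to a correlation of 0.9.

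**The full plan may settle it.** A condensed article commonly leaves a testing hierarchy to the full protocol or SAP, and the absence of one is not a fault in itself. The mismatch between 2.5 and the abstract, 2.3.2 and 2.9 lies within this article, however, and that stands. Measuring at week 1 is not an error either; its timing only argues against giving it primary weight.

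**Conclusion.** The point holds as an inconsistency over the primary test. The trial is sized on week 12, but the primary outcome is defined and tested at three weeks, each at 0.05, with none declared primary.

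Its size depends on a decision rule that the article does not give. If any week may support the claim, the two-sided family-wise error is about 8–14% for assumed correlations of 0.9 to 0. The matching figure for false claims of benefit is about 5–7% against 2.5%, for correlations of 0.8 to 0. If week 12 alone decides, the two-sided error is 5%.

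A flat statement that the trial runs a 10–14% risk of a false claim on its objective is tempting but not supported. It presumes the any-week rule, depends on correlations that the article does not give, and counts errors in both directions. The defect still merits correction, because it leaves open which result answers the primary question.

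**What to change.** In the abstract, 2.3.2 and 2.9, name one primary test: the between-arm difference in the proportion adherent at week 12, by chi-square at two-sided 0.05. Make weeks 1 and 6 secondary and report them as differences in proportions with 95% confidence intervals. A repeated-measures logistic model with arm, week and their interaction could supply all three estimates, but it is optional and not needed to cure the problem. Settle the choice before any between-arm results are seen, since a choice made afterwards cannot restore error control.

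**Cost.** Wording in three places, with the sample size unchanged. Success can no longer be claimed on week 1 or week 6 alone. Keeping all three weeks as primary with an adjusted threshold is possible, but Bonferroni would cut power per test from 80% to about 66% at the planned size.
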